## Abstract

**Background:**

In young children, bronchiolitis is the most common illness resulting in hospitalization. For children less than age 2, bronchiolitis incurs an annual total inpatient cost of $1.73 billion. Each year in the United States, 287,000 emergency department (ED) visits occur because of bronchiolitis, with a hospital admission rate of 32%-40%. Due to a lack of evidence and objective criteria for managing bronchiolitis, ED disposition decisions (hospital admission or discharge to home) are often made subjectively, resulting in significant practice variation. Studies reviewing admission need suggest that up to 29% of admissions from the ED are unnecessary. About 6% of ED discharges for bronchiolitis result in ED returns with admission. These inappropriate dispositions waste limited health care resources, increase patient and parental distress, expose patients to iatrogenic risks, and worsen outcomes. Existing clinical guidelines for bronchiolitis offer limited improvement in patient outcomes. Methodological shortcomings include that the guidelines provide no specific thresholds for ED decisions to admit or to discharge, have an insufficient level of detail, and do not account for differences in patient and illness characteristics including co-morbidities. Predictive models are frequently used to complement clinical guidelines, reduce practice variation, and improve clinicians’ decision making. Used in real time, predictive models can present objective criteria supported by historical data for an individualized disease management plan and guide admission decisions. However, existing predictive models for ED patients with bronchiolitis have limitations, including low accuracy and the assumption that the actual ED disposition decision was appropriate. To date, no operational definition of appropriate admission exists. No model has been built based on appropriate admissions, which include both actual admissions that were necessary and actual ED discharges that were unsafe.

**Objective:**

The goal of this study is to develop a predictive model to guide appropriate hospital admission for ED patients with bronchiolitis.

**Methods:**

This study will: (1) develop an operational definition of appropriate hospital admission for ED patients with bronchiolitis, (2) develop and test the accuracy of a new model to predict appropriate hospital admission for an ED patient with bronchiolitis, and (3) conduct simulations to estimate the impact of using the model on bronchiolitis outcomes.

**Results:**

We are currently extracting administrative and clinical data from the enterprise data warehouse of an integrated health care system. Our goal is to finish this study by the end of 2019.

**Conclusions:**

This study will produce a new predictive model that can be operationalized to guide and improve disposition decisions for ED patients with bronchiolitis. Broad use of the model would reduce iatrogenic risk, patient and parental distress, health care use, and costs and improve outcomes for bronchiolitis patients.

## Introduction

Bronchiolitis is inflammation of the bronchioles, the smallest air passages in the lungs, primarily seen in children less than age 2. Within the first year of life, 10% of children are diagnosed with bronchiolitis [1]. By age 2, more than a third of children have had a bronchiolitis diagnosis [2]. Bronchiolitis causes about 71 hospitalizations and 77 emergency department (ED) visits per 1000 infant years [3]. In the United States, each year bronchiolitis incurs around 287,000 ED visits [4], 128,000 hospitalizations [5], and $1.73 billion in total inpatient costs (2009) [5]. For children under age 2, bronchiolitis is the most common cause of hospitalization and represents 16% of all hospitalizations [5-8].

Despite the huge burden of bronchiolitis care, hospitalization decisions are made with insufficient evidence [7,9], resulting in variable admission rates [1,6,9-19]. About 32%-40% of ED patients with bronchiolitis are admitted to the hospital [20-22]. Studies suggest that 20%-29% of these admissions are unnecessary [23,24]. Unnecessary admissions waste health care resources, overwhelm hospital capacity, increase patient and parental distress, introduce iatrogenic risk such as exposure to other infectious diseases, and expose other hospitalized children to the respiratory pathogens of these patients [11,17,25]. As many as 10% of infants affected by bronchiolitis have adverse events while in the hospital [26]. Similarly, about 6% of ED discharges for bronchiolitis are unsafe, resulting in ED return with hospital admission [27] due to inadequate treatment [11]. New approaches are needed to improve ED disposition decision making and reduce unnecessary admissions and unsafe ED discharges.

One method to reduce practice variation and improve clinicians’ decision making for bronchiolitis care is to use clinical guidelines [28-31]. However, existing clinical guidelines for bronchiolitis acknowledge that decisions to admit or to discharge are subjective and rely on variable clinical judgment due to a lack of specific objective thresholds with good evidence [30,31]. Clinical guidelines also do not account for differences in patient and illness characteristics including comorbidities [32] and offer limited improvement in determining ED disposition.

Predictive models are an alternative method to reduce practice variation and improve decision making [20-22,33-35]. Predictive models can present objective criteria supported by historical data for an individualized disease management plan. Using data from previous patient encounters to identify patterns, predictive models [36] can overcome the limitations of clinical guidelines. Predictive models can be incorporated into electronic decision-support tools [37] to support the provisional judgment of clinicians or to trigger clinicians to reconsider their judgment in real time [20]. This is especially useful for physicians who see children infrequently or are junior. Typically when results of predictive models are provided, human experts can make better decisions [38].

As reported in our previous paper [39], existing predictive models for ED patients with bronchiolitis are limited by low accuracy and the assumption that actual ED disposition decisions were appropriate. No operational definition of appropriate admission of ED patients with bronchiolitis exists and no model has been built on appropriate admissions (Figure 1). To fill the gap, we will meet the following 3 aims: (1) develop an operational definition of appropriate hospital admission for bronchiolitis, (2) develop a new model to accurately predict appropriate disposition for ED patients with bronchiolitis, and (3) conduct simulations to estimate the impact of using the model on outcomes.

**Figure 1 figure1:**
[figure not shown]
The definition framework of appropriate admission versus appropriate ED discharge that was provided in our previous paper [39]. The details denoted by ""? will be determined by direct evidence in this current study.

### Innovations

This study makes the following innovations within the context of bronchiolitis:

We will develop a new approach to construct an operational definition of appropriate hospital admission in the ED based on objective data rather than clinical judgment. No such approach currently exists.We will figure out the most important attributes to put into the predictive model using a new simulation method. We will use various attribute combinations to ascertain the minimum requirement on performance and permit tradeoffs for the adaption of our model beyond our setting dependent upon available attributes. Current models are not generalizable beyond the study site because they rely on a certain set of attributes that may be nonexistent in different electronic medical records.We will build the first model to accurately predict appropriate admission for ED patients with bronchiolitis in real time. No such model currently exists. We will transform bronchiolitis care by developing a predictive model to guide appropriate admission for the first time.Our model will increase prediction accuracy by using a rich set of extracted attributes, including known predictors of hospital admission not used in existing models for ED patients with bronchiolitis.Our model will include environmental variables with a potential for a further increase in accuracy. Air quality environmental variables are associated with the daily number of hospitalizations for bronchiolitis [40] and a child’s risk of hospitalization for bronchiolitis within the first year of life [41]. The predictive power of air quality and respiratory virus environmental variables for appropriate admission has never been evaluated.Our study will evaluate the impact of using the model on outcomes. Previous predictive models focused only on accuracy. No impact estimate of using the model on bronchiolitis outcomes has ever been provided.We will use a large data set of 26,701 bronchiolitis patients with high potential to achieve high prediction accuracy. Previous studies are limited by small data sets with typically far fewer than 1000 patients. Many useful predictors of hospital admission cannot be identified in small data sets.

In summary, this study is significant as it will fill gaps by developing a new model to guide and improve disposition decisions for ED patients with bronchiolitis. Broad use of the model will reduce iatrogenic risk, patient and parental distress, health care use and cost, and improve clinical outcomes for bronchiolitis patients. A future study will test the impact of using the model in a randomized controlled trial after implementing the model in an existing electronic medical record to facilitate real-time decision making.

## Methods

Machine learning is a field that studies the automatic improvement of computer algorithms with experience. Machine learning methods—such as support vector machine, neural network, and decision tree—are commonly used in predictive modeling [36] and will be adopted in our study. In comparison to statistical methods, machine learning can improve prediction accuracy, occasionally doubling it, with less stringent assumptions on data distribution [38,42,43].

For all 3 aims, we will use the same patient population and data sets:

Patient population: Our study cohort includes children under age 2 who had ED encounters at 22 Intermountain Healthcare facilities for bronchiolitis (ICD-9-CM discharge diagnosis code 466.1 [4]) in the past 10 years. Intermountain Healthcare is the biggest health care system in Utah, comprising 185 clinics and 22 hospitals.Data sets: A large administrative and clinical data set in the enterprise data warehouse (EDW) of Intermountain Healthcare will be used. The Intermountain Healthcare EDW contains a vast set of attributes [44]. Our Intermountain Healthcare data analyst will run SQL queries to obtain a data set that has been de-identified and encrypted and then securely transfer it to a computer that is encrypted and password-protected. Secondary analysis will be conducted on the computer. Intermountain Healthcare has dedicated tables to identify changes in procedure and diagnosis codes. The data set contains electronic documentation of about 85% of pediatric care delivered in Utah [45] and includes approximately 400 attributes. A partial list of categories of these attributes includes: admission date and time; age; orders (eg, medications, labs, exams, immunizations, imaging, counseling, etc), including order name, ordering provider, performing date, and result date; allergies; chief complaint; diagnoses; discharge date; exam result; facility seen for the patient visit; gender; health insurance; health care cost (billed charge, Intermountain Healthcare internal cost and reimbursed cost); height; home address; immunizations; lab test result; language(s) spoken; medication refills; primary care physician as listed in the electronic medical record; problem list; procedure date; procedures; provider involved in the visit; race/ethnicity; referrals; religion; visit type (inpatient, outpatient, urgent care, or emergency department); vital signs; and weight [46].

For the last 5 years, data captured cover more than 2900 patients under age 2 and 3500 ED encounters for bronchiolitis per year. Due to its attribute richness and large size, the data set provides many advantages in the exploration of the proposed predictive models. Furthermore, we will use 21 environmental variables that regional monitoring stations recorded over the past decade within the Intermountain Healthcare region. These variables include carbon monoxide, nitrogen dioxide, particulate matter up to 2.5 μm in size and 10 μm in size, ozone, sulfur dioxide, relative humidity, temperature, precipitation, wind speed, dew point, and activities of each of the following viruses: enterovirus; adenovirus; parainfluenza virus types 1, 2, and 3; human metapneumovirus; influenza A and B viruses; rhinovirus; and respiratory syncytial virus. The data for all nonvirus environmental variables came from federal data sources [47,48], which provide such data throughout the United States. Observation unit admissions will be treated as hospital admissions since the only pediatric observation unit within Intermountain Healthcare has the same admission, coding, billing, and documentation requirements. Our analysis will consider various attribute combinations to ascertain the minimum requirement on performance and will permit tradeoffs for the adaption of our model beyond our setting dependent upon available attributes. Our analysis results will serve as the basis for future expansion of our models to other clinical data sets and diseases beyond bronchiolitis.

### Aim 1: Develop an Operational Definition of Appropriate Hospital Admission for ED Patients with Bronchiolitis

In a recent paper [39], we provided a definition framework of appropriate hospital admissions. As shown in Figure 1, we equate appropriate admissions to necessary admissions and unsafe discharges. We equate appropriate ED discharges to safe discharges and unnecessary admissions. The definition uses several threshold values, such as the maximum number of hours for which major medical interventions are used. Using a data-driven approach, we will fill in these values and develop an operational definition to be used in Aims 2 and 3.

For unsafe discharges, we will examine the distribution of the interval between discharge from the ED and a return visit resulting in admission for bronchiolitis within the period of 2 weeks [49,50]. The 95th percentile of the interval will cover most readmissions and define the return threshold for unsafe discharge. The distribution is highly skewed toward a short interval [27]. Thus, the return threshold will be insensitive to the length of the period chosen.

For unnecessary admissions, we will examine the patients who stayed in the hospital for 12 hours or less and were discharged without readmission for bronchiolitis within 2 weeks. These patients are likely to have been admitted unnecessarily. Their median duration of using major medical interventions (Figure 1) will serve as a conservative threshold for use of major medical interventions in all admissions. Unnecessary admissions are those with major medical intervention exposures for no longer than the threshold. We will conduct sensitivity analysis to evaluate the impact of interactions between major medical interventions and other variables.

If the operational definition for all bronchiolitis patients lacks face validity, we will examine data distributions for different age groups to obtain operational definitions by age group. Since the medical interventions for bronchiolitis have not changed over the last 10 years, we would expect the operational definition to remain the same during this period.

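### The no-readmission condition used to derive the exposure threshold is dropped from the final rule for unnecessary admissions, so a readmitted low-exposure child is labelled as suitable for ED discharge

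*Protocol article*

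**What the plan says.** All of this stands in the Methods of the protocol article, under Aim 1.

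- **Label structure.** On one side, "we equate appropriate admissions to necessary admissions and unsafe discharges". On the other, "We equate appropriate ED discharges to safe discharges and unnecessary admissions".
- **Unsafe discharge.** The study looks at "the interval between discharge from the ED and a return visit resulting in admission for bronchiolitis within the period of 2 weeks". The cut-off is then set: "The 95th percentile of the interval will cover most readmissions and define the return threshold for unsafe discharge".
- **Source of the exposure threshold.** The patients examined are those who "stayed in the hospital for 12 hours or less and were discharged without readmission for bronchiolitis within 2 weeks". The article regards them as probably admitted without need. Their median duration of major medical interventions becomes the threshold, which is then used for every admission.
- **Final rule.** "Unnecessary admissions are those with major medical intervention exposures for no longer than the threshold". Readmission is not mentioned here.

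The labels are used twice. In Aim 2 they are the two values of the dependent variable. In Aim 3 (Estimate a Model's Impact) they divide the tenth-year visits into necessary admissions, unnecessary admissions, unsafe discharges and safe discharges.

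**The concern.** The derivation group is credible as a picture of unneeded admission for two reasons together: the stay was short, and the child did not come back. The final rule keeps a number computed from that group but drops the second reason. It thus extends the label to children whose later course is evidence against it.

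The result is also uneven across dispositions. After an ED discharge, a return admission inside the window shows that the discharge was unsafe. After a low-exposure admission, the same event does not count, and the visit is filed with the appropriate ED discharges.

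For such a visit, a model that suggests discharge is scored as correct in Aim 2. In Aim 3 the visit falls outside the necessary-admission group, where the article assumes that a wrongly suggested discharge leads to an unsafe discharge, an early return and the associated cost. The misclassification therefore favours the model, if only slightly. No planned check would reveal it: the Aim 1 sensitivity analysis concerns interactions between interventions and other variables, and the fallback for poor face validity only splits the definition by age group.

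**Working it through.** The point is one of logic, and the plan states no figure to reproduce for it. The first step traces the rules; the second illustrates the size.

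**Step 1. Same later course, two dispositions**

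| | Child X | Child Y |
|---|---|---|
| ED disposition at index visit | Discharged | Admitted, exposure at or below threshold |
| Later course | Admitted for bronchiolitis within the return window | Readmitted for bronchiolitis within the return window |
| Rule applied | Return with admission | Exposure only |
| Group | Unsafe discharge | Unnecessary admission |
| Label | Appropriate admission | Appropriate ED discharge |

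Child Y could not have contributed to the threshold, because readmission within 2 weeks excludes a child from the derivation group. The threshold is nevertheless applied to Child Y.

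**Step 2. Illustrative size in the tenth year**

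Inputs from the article:
- 3615 tenth-year ED visits (Aim 2, Sample Size Justification and Performance Evaluation).
- 32% to 40% of ED patients admitted (Introduction).
- 20% to 29% of admissions unnecessary: "Studies suggest that 20%-29% of these admissions are unnecessary" (Introduction). This is a literature range, not one measured with this study's threshold.

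Assumed input: 1% to 6% of unnecessary admissions are readmitted within the window. The article gives no such rate.

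Formula: affected visits = visits × admission rate × unnecessary share × readmission rate.

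- Unnecessary admissions, low end: 3615 × 0.32 × 0.20 = 231.
- Unnecessary admissions, high end: 3615 × 0.40 × 0.29 = 419.
- Affected visits, low end: 231 × 0.01 = about 2.
- Affected visits, high end: 419 × 0.06 = about 25.
- Share of all visits: 2/3615 = 0.06% to 25/3615 = 0.7%.

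The right denominator within a class is the unnecessary admissions, where these visits sit. There the share is simply the assumed 1% to 6%.

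**The case against.** **Figure 1 may already hold the condition.** The definition framework is in that figure, which is not visible here, and the Aim 1 text is partly an account of how its blanks will be filled. This stands as a caution. It does not remove the point, because the text states the final rule outright and without the condition; if the figure has it, the two disagree.

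**A readmission is an imperfect sign that the ED was right to admit.** It comes after a hospital stay and may reflect the inpatient discharge decision. This also stands. It is a reason to report the affected visits openly, but the authors themselves treated absence of readmission as part of what makes an admission look unneeded.

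**A stronger reading is tempting: that the two label rules contradict each other outright.** A reader might infer this from a child who is discharged, returns, and is admitted with exposure at or below the threshold. The first visit then counts as an appropriate admission and the second as an appropriate ED discharge. The article does not support calling this a contradiction. One rule covers visits that end in discharge and the other visits that end in admission, so no visit receives two labels. The Introduction itself describes unsafe discharges as those that result in ED return with admission. Taking any return admission as the signal is a debatable proxy, and the more cautious one.

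Requiring the return admission to exceed the exposure threshold would have a real price. With 6% of discharges unsafe, 3615 × 0.60 × 0.06 = 130 to 3615 × 0.68 × 0.06 = 147 visits are in that group. If 20% to 29% of their return admissions were low-exposure, which is an assumption, 26 to 43 would be relabelled as safe. If any readmission, whatever its exposure, also cancelled an unnecessary label, low-exposure returns would be treated differently in the two places.

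**Conclusion.** The point holds for the unnecessary-admission rule. As written, the rule is broader than the group that justifies it, and it labels some readmitted children as appropriate ED discharges.

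The likely size is small: about 2 to 25 of 3615 tenth-year visits. This rests on an assumed 1% to 6% readmission rate and on literature rates for admission and unnecessary admission. The reason to act is that the rule defines the reference standard for both later aims and costs little to correct.

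Two further inferences are not supported. The affected visits do not fall in the unsafe-discharge class; they are among the roughly 231 to 419 unnecessary admissions. Nor does anything in the article show that so few visits would noticeably change the AUROC, the cost result or what the model learns to recommend.

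**What to change.** 1. Carry the condition into the final rule: an admission is unnecessary only if exposure is at or below the threshold **and** no readmission for bronchiolitis follows within the return threshold. State that the interval runs from hospital discharge, since the return threshold is derived from ED discharges.
2. If Figure 1 already contains the condition, bring the text into line with it.
3. Report how many labels change.
4. As a sensitivity analysis only, count the unsafe discharges whose return admission itself falls at or below the exposure threshold. Leave the primary unsafe-discharge rule unchanged.

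The cost is one clause and two counts, using visit and intervention data that the study needs for its own definitions. The downside is slightly fewer unnecessary admissions, some of them moved because of a readmission that may reflect the inpatient discharge rather than the ED disposition.
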